## Discussion

This study leverages interventions that are clinically effective in an already-established wellness program in Guam and tested them for the first time in a randomized controlled trial. The main goal of the study was to determine the effectiveness of an intensive lifestyle intervention consisting of a mostly plant-based diet and regular moderate exercise in Marshall Islanders with T2D. We expected that study participants would be able to adopt a plant-based diet and engage in moderate exercise sufficiently to achieve clinically meaningful improvements in glycemic control and that many participants would reduce their reliance on diabetes medications and/or even potentially go into remission from T2D. We also expected that participants would experience improved lipid profiles, reduced blood pressure, and lower levels of inflammation, relative to the standard of care. To support these objectives, we leveraged ongoing organizational networks within the RMI, including Canvasback Missions' more than 11 years of experience in providing medical services to T2D patients in the RMI. Moreover, we forged partnerships with the local government to deliver a culturally-adapted version of an intensive lifestyle intervention using trained indigenous staff.

Through implementing this clinical trial, we achieved several major community-wide successes, which serve as a model for future lifestyle intervention trials and community-based participatory research. One of the major achievements is that we assisted in designing an expanded and improved 6,700-square foot Diabetes Wellness Center, which has now been established and is operating in Majuro. The intervention itself was so successful that supermarket buying patterns in Majuro have changed. Reports from the local supermarket indicate that the demand for healthy foods has increased to such an extent that these items are “gone in 2–3 days.” The DWC received many requests to speak and present intervention programs for churches, schools, and service groups. The DWC also held a seminar for the members of the Nitijela (Parliament) and the president's cabinet. As a result of the influence of these leaders, the community has begun to respond by changing their food choices and exercising more. When DWC staff first arrived in Majuro, walking was frowned upon, and people tended to take taxis, even for short distance outings. Now, walking for exercise has become sufficiently popular that there are concerns for public safety, as most walking takes place on the roads. As a result, the mayor and police commissioner have agreed to close down the main highway in the early morning to provide the community with a safe place to walk during the cooler dawn hours. More markets are setting aside sections for health foods, and the island now has a good selection of these foods. Produce is being flown in to meet the new public demand. DWC-approved items are appearing on local restaurant menus. The MOH has asked Canvasback Missions to take over food preparation for the hospital. The Department of Education approached Canvasback Missions to develop a nutrition curriculum for grades K-6 in public schools in Majuro and to train teachers. Canvasback Missions was awarded a grant from the World Diabetes Federation. [name], RD and [name], SLP, were recently brought into Majuro to complete this work. They developed a comprehensive 13-module curriculum called *Get Healthy at School*. Teachers in all nine public schools in Majuro were trained to use these materials in their classrooms. The MOH also held a 2-day conference with its senior administrative staff and leading doctors to find ways to focus on preventive health care. Word of the success of this program has reached many of the surrounding Pacific Island jurisdictions, and the DWC often hosts visitors from these countries.

In achieving these successes, we overcame several challenges. First, recruitment was slower than expected in year 1, so in year 2, we increased enrollment rates by recruiting subjects from the MOH Diabetes Clinic. Another benefit of this change in our recruitment strategy is that it improved compliance to the standard of care in the control group. During year 1, when participants were screened from the general public, they did not always adhere to the standard of care. Recruiting subjects who were already receiving the usual care and regularly met with their physicians resolved this problem. In year 2, as the word spread throughout the country that the DWC program was controlling and reversing T2D naturally, more and more people came forward and wanted to participate, and recruitment was no longer a challenge. In fact, by the end of the trial, more than 100 people were on the waiting list for the DWC program. Another challenge faced in year 1 is that about 25% of the adults screened did not comprehend English well enough to understand materials presented in English. This may have introduced selection bias by enrolling better-educated participants in year 1. Therefore, in year 2, all program materials were translated into Marshallese and presented in Marshallese, initially by translating English presentations, and then later by replacing English presentations with Marshallese presentations. Cohort 5 was the first all Marshallese-run program. After an initial hurdle of training local staff, who had little previous experience and limited education, to become precise and accurate recordkeepers and accurate presenters, we were able to deliver an all Marshallese-version of the intervention.

As for the intervention itself, we observed that the 4-times-per-week intensive phase appeared to be highly effective in promoting adherence to the lifestyle intervention and improving glycemic control. However, once the intervention intensity dwindled to once-every-other-week, a majority of participants did not maintain adherence as well, so adherence waned in the later stages of the trial. This may partially be due to the fact that intensive lifestyle changes can be socially and culturally isolating, particularly because the RMI is a highly social and culturally engaged society, where food is often a central part of cultural events. After some trial and error, we noticed that moving from a 4-times-per-week intensive phase to a twice-per-week phase (rather than every other week) is a more effective approach. It is important for future trials on intensive lifestyle interventions to continue testing the optimal intensity of lifestyle interventions. One of the main unanticipated effects of the intervention is that a significant fraction of the control group attempted the intensive lifestyle program on their own, despite being randomized to the standard of care. Such participants were spotted purchasing foods, such as oatmeal and flaxseeds, at the grocery store, despite not having used these foods before; some of these participants admitted that they were trying to do the lifestyle intervention on their own. In total, we estimate that about one-fourth of the controls adopted significant lifestyle changes during the 24-week intervention, despite instructions to the contrary and despite having the opportunity to crossover to the intervention group after completing the control arm. Contamination of the control group tends to bias outcomes toward the null hypothesis, so our anticipated future results may underestimate the actual treatment effects. Another intervention-related concern is the potential for nutritional shortfalls, especially regarding vitamin B12. Although we used some vitamin B12-fortified foods, such as nutritional yeast and fortified soymilk, such fortified foods are not as readily available in the RMI, and there was concern that over time, vitamin B12 intakes could be inadequate, especially for participants taking metformin. Also, healthy foods, such as fruits and vegetables, are expensive in the RMI, and residents tend to have few resources.

The management of adverse events and data collection in a country with no prior research infrastructure presented the greatest challenges to the trial. The main challenge for adverse event management was adjusting medication dosages downwards to avoid hypoglycemic reactions in the intervention group. When participants were not in the clinic, they often had to return to their family physician to adjust their medication dosages, which meant long wait times and a fee. This was particularly problematic for participants on insulin, who had to be very carefully monitored so that insulin dosages could be reduced or stopped accordingly. Further, because medication dosing tended to increase for control subjects and decrease for intervention subjects, future reported outcomes will likely be biased toward the null hypothesis. We also faced problems with missing data due to participants not showing up for appointments, procedural failures by the laboratory, and the hospital being new to the extensive documentation requirements for clinical trials, in a country where clinical trials have never been performed before. It took several trips and digging through boxes of duplicate lab slips to fill in missing logbook entries. The positive outcome is that new policies and reporting procedures were established for any future lab work that may be required, and all lab work that was done is now backed up. To tackle the challenge of participant attendance at clinic visits, research staff attempted to reach every participant by phone, and in some cases, went to the participant's home or work to remind them of the importance of the blood draws and measures to complete the study. We have discovered that within the RMI, more effort is needed than in the U.S. to ensure that participants fully participate in the intervention.

Overall, though, the clinical trial was a success. We delivered a novel lifestyle intervention, which constituted the first randomized clinical trial conducted in the Republic of the Marshall Islands; the first lifestyle intervention trial conducted in Micronesia; and the second clinical trial to investigate the effects of a plant-rich diet combined with moderate exercise in T2D patients. We intend to publish future manuscripts reporting the results of the clinical trial. We expect that the results of this study will help guide future medical care in the Pacific Islands and provide insight into how to best direct resources to treat indigenous populations with T2D. Outside of the Pacific Islands, it will shed light on how to effectively deliver comprehensive, intensive lifestyle interventions for the treatment and management of diabetes. Finally, it will provide critical insight into the degree to which lifestyle interventions can treat and reverse type 2 diabetes.

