#### Recruitment

During year 1 of the study, participants were initially recruited from the general public. Two local leaders assisted in building interest among and recruiting Majuro residents. During year 2, participants were recruited both from the general public and from the MOH Diabetes Clinic through its diabetes registry. Of those screened, 18% or 31 out of 169 eligible participants dropped from the trial before beginning the intervention. The first cohort began the study intervention in June 2006 and the last cohort began in July 2008. Due to a lack of funding after the clinical trial ended, the study data was not analyzed and published until the present.

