#### Medications

To monitor changes in glucose levels in the intervention group and adjust medication dosages accordingly, a glucometer was used during the first 2 weeks and fasting labs at weeks 2, 6, and 12 were relied on thereafter. Medication dosages were adjusted by participants' primary care physicians and/or the DWC clinicians. Medications and their dosages were recorded at each assessment. Changes in the average number of medications and in the percentage of participants taking one or more medications will be compared across groups for both all medications and diabetes-specific medications.

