### Statistical Analyses

All data will be analyzed using two-sided statistical tests and a Type I error rate of α = 0.05. The intention-to-treat method will be used for the primary analyses but will be compared to outcomes from actual-treatment-received analyses (i.e., per protocol analyses). Categorical data will be compared between the two groups using chi-square or Fisher's exact tests. Continuous data will be compared using linear mixed models or non-parametric tests (as appropriate), with potential adjustments for changes in medication dosages and potential covariates such as baseline values, age, biological sex, and cohort number. Likelihood functions will be examined to determine the appropriateness of covariates and to avoid overfitting the data. Multivariable linear and logistic regression will be used to identify predictors for improved health outcomes. Lastly, subgroup analyses may be performed by sex, age, co-morbidity, length of diagnosis, and severity to evaluate heterogeneity in treatment responses.

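### The primary test, the covariates and an adjustment for medication change are still open after the trial ended, and the article already states how dosing moved in each arm

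*Protocol article*

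**What the plan says.** All places are in the protocol article.

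- **Timing and blinding.** Study Overview says the trial was open-label and not blinded. Recruitment says: "The first cohort began the study intervention in June 2006 and the last cohort began in July 2008". It adds: "Due to a lack of funding after the clinical trial ended, the study data was not analyzed and published until the present".
- **Endpoints.** The Introduction lists five primary endpoints: fasting glucose, fasting insulin, HbA1c, HOMA-IR and usage of diabetes medications.
- **Analysis.** Statistical Analyses fixes two-sided tests at 0.05 and intention-to-treat for the primary analyses. For the rest it says: "Continuous data will be compared using linear mixed models or non-parametric tests (as appropriate), with potential adjustments". The possible adjustments are changes in medication dosages and covariates such as baseline value, age, sex and cohort number. Covariates are to be judged by examining likelihood functions.
- **Medication endpoint.** Medications says: "Changes in the average number of medications and in the percentage of participants taking one or more medications will be compared across groups". The same section says that, in the intervention group, doses were adjusted in response to glucose measurements.
- **What was already known.** The Discussion expects outcomes to be biased toward the null "because medication dosing tended to increase for control subjects and decrease for intervention subjects". It also says that "the 4-times-per-week intensive phase appeared to be highly effective in promoting adherence to the lifestyle intervention and improving glycemic control".

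**The concern.** Leaving the model open in a condensed article would normally be unremarkable. Two features change that here.

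First, the choices are still worded as open after follow-up had ended in an unblinded trial. One of the optional adjustment variables, change in medication dosage, is the variable whose movement by arm the Discussion reports, together with its expected effect on the outcomes. Whoever decides whether to adjust for it already holds a view of which way the decision pushes the glucose and HbA1c results.

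Second, that variable is affected by treatment and by glycaemia. Putting it in the model is not a neutral gain in precision: it changes what the arm coefficient estimates. If the adjusted version became the headline result, it would no longer be the intention-to-treat contrast that the same section calls primary.

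At stake are the primary claims on the continuous glycaemic endpoints. A p-value below 0.05 would be hard to interpret if the reader cannot tell which permitted analysis was primary, or when that was settled.

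**Working it through.** **1. Timing.** The last cohort began in July 2008. Adding 24 weeks (168 days) puts the end of follow-up between mid-December 2008 and mid-January 2009. The analysis text, in the future tense, appears in an article written after that. The article gives no date for when the analysis choices were fixed.

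**2. Cost of free choice among permitted analyses.** The cohort sizes in Cohorts sum to 13 + 21 + 9 + 14 + 22 = 79 (intervention) and 14 + 20 + 22 + 13 + 21 = 90 (control), 169 in all. Data were simulated with no effect for one continuous endpoint at one visit. Assumptions, not from the article: baseline correlation 0.5 or 0.7, small age and sex effects, between-cohort SD 0.3 (in outcome SD units). The seven analyses were arm only; plus baseline; plus baseline, age and sex; plus baseline and cohort; all of these; a rank test on the value; and a rank test on the change.

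| Rule for choosing the analysis | Rejections at 0.05 |
|---|---|
| One fixed model (arm, baseline, cohort) | 4.7 to 5.5% |
| Covariate set chosen by likelihood criterion (AIC or BIC) | 5.1 to 5.6% |
| Smallest p-value of the seven | 12.4 to 13.4% (6,000 and 5,000 replicates); 11.5 to 11.6% in a run with different nuisance effects (4,000) |

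The Monte Carlo standard error at 13% with 6,000 replicates is √(0.13 × 0.87 / 6000) = 0.0043, or about 0.4 percentage points. The third row assumes that the most favourable result is always reported, so it is an upper bound. The second row is closer to the covariate rule the article states, but it does not cover the choice between mixed model and rank test, or the medication adjustment.

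**3. The medication adjustment.** Let τ be the total (intention-to-treat) effect of arm on the outcome, δ the difference in medication change (intervention minus control), and γ the slope of the outcome on medication change within arm. In linear models the arm coefficient after adjustment is

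τ − γδ.

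With no total effect (τ = 0) it equals −γδ, which is zero only if γ or δ is zero. The Discussion indicates δ < 0. Two cases follow for γ:

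- If more medication lowers glucose and this dominates, γ < 0. The adjusted coefficient is then negative, which favours the intervention. This matches the article's statement that unadjusted outcomes lean toward the null.
- If higher glucose prompts more medication and this dominates, γ > 0 and the shift goes the other way. Medications shows that such a response existed in the intervention group.

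Simulating medication change as dependent on both arm and glycaemia, with assumed sizes and no total effect, the adjusted model rejected in 11 to 14% of trials. The fixed model without it rejected in about 5%. The 11 to 14% depends on the assumed γ and δ, for which the article gives no figures; it shows that the problem exists without estimating its size in this trial.

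**The case against.** The strongest reply is that the article's date is not the plan's date. Two review boards approved the study, and a fuller protocol or analysis plan may have fixed the model earlier. That stands: the document does not show that the choices were made after anyone saw the data.

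A reader might infer that results by arm were known. The text does not go that far. Recruitment says the data had not been analysed until the present. The remark on glycaemic control in the intensive phase is an impression of the programme, not a between-arm comparison. The year 1 data in Statistical Power Calculation are described only as variances.

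A reader might also infer that the direction of the medication endpoint is already printed. The Discussion speaks of dosing, whereas Medications compares the number of medications and the percentage of participants taking any. These are related, but a dose can fall while neither measure changes.

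A third reply is that the inflation in step 2 needs deliberate selection on the p-value, since the stated likelihood rule leaves the error near 5%. That also stands, and it limits how far the 12 to 13% can be pressed.

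These replies do not reach the medication adjustment. It is named as an option, its by-arm trend and expected effect are in the same article, and it distorts the primary contrast even if chosen in good faith.

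**Conclusion.** The concern holds in a limited form. In an open-label trial that had ended, the article leaves the test, the covariates and an adjustment for medication change open at 0.05. At least the last can be chosen knowing its expected direction. It is also a post-randomisation variable that should not enter the primary intention-to-treat model.

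For one endpoint, free choice among seven permitted analyses costs at most about 12 to 13% false positives instead of 5%. Covariate choice by likelihood alone costs almost nothing. Adjusting for medication change rejected in 11 to 14% under no total effect, with assumed effect sizes.

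The documents do not support the stronger conclusion that the tests are not confirmatory, because an earlier dated plan may exist. Nor do they support demoting diabetes medication usage. It is a listed primary endpoint, and removing it because a related trend is known would itself be a data-driven change.

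**What to change.** In Statistical Analyses:

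1. State when the analysis choices were fixed, relative both to access to the data and to knowledge of the by-arm dosing trend given in the Discussion. If an earlier dated plan exists, one sentence citing its date is enough for this item.
2. Name one primary analysis for each continuous primary endpoint: the intention-to-treat linear mixed model with baseline value and cohort as fixed covariates, and no adjustment for medication-dose change. Cohort belongs in the model because Cohorts says randomisation was done within cohort.
3. Label the medication-adjusted, non-parametric and other covariate versions as sensitivity analyses, and report all of them side by side whatever they show.
4. Keep diabetes medication usage as a primary endpoint. Report it with an estimate and confidence interval, and note that the by-arm dosing trend was known.

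The cost is some wording and one extra results table. The analysts lose the freedom to choose the final model. No new data are needed, and the Discussion says the results papers are still to come.

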## Ethics Statement

The study was approved by the Loma Linda University Institutional Review Board and an *ad-hoc* Institutional Review Board in the RMI that was set-up specifically for the trial. The raw data may be requested by contacting the corresponding author, [name], at [contact], after the study results are published. The data request will be reviewed by the RMI Ministry of Health.

## Abbreviations

T2D: Type 2 diabetes
RMI: Republic of the Marshall Islands
BMI: body mass index
HbA1c: hemoglobin A1c
HOMA-IR: Homeostatic Model Assessment of Insulin Resistance
hs-CRP: high-sensitivity-C-reactive protein
MOH: Ministry of Health
DWC: Diabetes Wellness Clinic
NEWSTART: Nutrition, Exercise, Water, Sunshine, Temperance, Air, Rest, and Trust in divine power.
